## Abstract

**Background:**

Perforated diverticulitis is a condition associated with substantial morbidity. Recently published reports suggest that laparoscopic lavage has fewer complications and shorter hospital stay. So far no randomised study has published any results.

**Methods:**

DILALA is a Scandinavian, randomised trial, comparing laparoscopic lavage (LL) to the traditional Hartmann's Procedure (HP). Primary endpoint is the number of re-operations within 12 months. Secondary endpoints consist of mortality, quality of life (QoL), re-admission, health economy assessment and permanent stoma. Patients are included when surgery is required. A laparoscopy is performed and if Hinchey grade III is diagnosed the patient is included and randomised 1:1, to either LL or HP. Patients undergoing LL receive > 3L of saline intraperitoneally, placement of pelvic drain and continued antibiotics. Follow-up is scheduled 6-12 weeks, 6 months and 12 months. A QoL-form is filled out on discharge, 6- and 12 months. Inclusion is set to 80 patients (40+40).

**Discussion:**

HP is associated with a high rate of complication. Not only does the primary operation entail complications, but also subsequent surgery is associated with a high morbidity. Thus the combined risk of treatment for the patient is high. The aim of the DILALA trial is to evaluate if laparoscopic lavage is a safe, minimally invasive method for patients with perforated diverticulitis Hinchey grade III, resulting in fewer re-operations, decreased morbidity, mortality, costs and increased quality of life.

**Trial registration:**

British registry (ISRCTN) for clinical trials ISRCTN82208287http://www.controlled-trials.com/ISRCTN82208287

## Background

Complicated diverticulitis sometimes requires emergency surgery with considerable morbidity [1]. It is classified by severity according to the Hinchey grading scale, where I and II represent contained abscesses, and III and IV are cases with perforated colon and purulent (III) or faecal (IV) leakage [2]. The traditional treatment for the Hinchey III and IV has been open surgery with resection of the affected segment, blind closure of the distal resection line and a diverting colostomy i.e. Hartmann's procedure [3-6]. Another option is resection with primary anastomosis of the colon [3]. A retrospective study at the Sahlgrenska University Hospital, Gothenburg studied all patients (n = 106) admitted and operated for complicated diverticulitis between 2003 and 2008 [7]. Eighteen percent underwent at least one re-operation during their first admission, and the mean length of hospital stay was 17 (1-111) days. Mortality was 6%, not different from similar studies [2,6]. The number of complications indicated considerable suffering, morbidity and resource consumption [7]. Only 56% of patients operated with Hartmann's procedure later underwent surgery for stoma reversal [7]. Other studies have shown that the reversal of Hartmann's Procedure alone has a morbidity rate of 20% (3-39) and mortality of 1-6%[8,9].

Several recently published reports suggest a new principle for the treatment of perforated diverticulitis, consisting of laparoscopy, lavage and drainage without colon resection [10-16]. One prospective study including 92 patients with laparoscopic lavage showed morbidity and mortality rates of 4% and 3%, respectively. No re-intervention was needed. Eighty-nine patients recovered without morbidity and resumed oral intake after 2 days (1-9) and were discharged after 8 days (7-19)[17].

Janson et al [17] have shown that laparoscopic resection for colon cancer results in a higher quality of life compared to open surgery, and although there is little evidence indicating laparoscopy being more cost-effective than open surgery [18], a recent Health Technology Assessment suggests that there are economical benefits to lavage of perforated purulent diverticulitis, due to decreased surgical measures and shorter length of hospital stay [19]. With this in consideration there are several factors in favour of the new treatment, laparoscopy and lavage.

Randomised studies are required before laparoscopic lavage can be proven to be the therapy of choice in perforated diverticulitis Hinchey grade III [19]. This is a description of a randomized trial for complicated diverticulitis initiated in Scandinavia.

## Methods

### Study Objective

The DILALA-trial is a randomised trial comparing laparoscopic lavage to Hartmann's Procedure, 1:1, as treatment for acute perforated diverticulitis.

### Endpoints

Primary endpoint is number of re-operations within 12 months from the initial emergency operation.

Secondary endpoints include re-admissions, postoperative wound or deep infections, postoperative thrombosis, hernia, bowel obstruction requiring hospitalisation or operation, other complications, total length of hospital stay (for diverticulitis and complications) during 12 months, quality of life, health economy analysis, mortality within 30 days of the primary operation, mortality within 12 months, permanent stoma, re-admissions and re-operations registered in the hospital database at 24 months.

### Inclusion Criteria

Inclusion criteria to diagnostic laparoscopy

• Clinical symptoms (left lower quadrant pain, peritonitis)

• Elevated body temperature

• Elevated C-reactive protein and leukocyte count.

• Radiology showing signs of free gas and/or intraabdominal fluid

• Emergency surgery decided by the attending surgeon

• Possible to operate in regard to concomitant disease

• Informed consent

### Randomisation Criteria

• Hinchey grade III at diagnostic laparoscopy, i.e. free fluid

### Excluded From Randomization

• Hinchey grade I - II at laparoscopy i.e. no free fluid

• Hinchey grade IV at laparoscopy, i.e. gross faecal contamination

• Other pathology than diverticulitis diagnosed as explanation of peritonitis

The Hinchey grading [2]

**Stage Ia: **Phlegmonae

**Stage Ib: **Diverticulitis with peri-colic or mesenteric abscess

**Stage II: **Diverticulitis with walled-off pelvic abscess

**Stage III: **Diverticulitis with generalised purulent peritonitis

**Stage IV: **Diverticulitis with generalised faecal peritonitis

### External Validity

All patients with acute diverticulitis considered for emergency surgery are registered in the "screening log" at each participating centre. Patients who do not meet the inclusion criteria, as well as included but not randomised patients or patients excluded after randomisation are registered.

### Randomisation and Surgical Procedure

Patients are considered for inclusion when surgery is required. The operation starts with a diagnostic laparoscopy. All four quadrants of the abdomen must be visualised to ascertain no other or concomitant pathology. Patients are randomised when the diagnosis of diverticulitis Hinchey grade III has been confirmed. Randomisation is 1:1 to laparoscopic lavage and Hartmann's Procedure. Hinchey grade I, II and IV are excluded from randomisation and treated according to local guidelines.

Patients randomised to lavage receive at least 3L of body-temperature, until return of clear fluid. A passive drainage is placed in the pelvis for at least 24 h, and antibiotics are continued postoperatively according to local guidelines.

Patients randomised to Hartmann's Procedure are converted to open surgery followed by resection of the inflamed part of the colon and a diverting colostomy. A passive drainage is placed in the pelvis for at least 24 h, and antibiotics are continued postoperatively according to local guidelines (Figure 1).

**Figure 1 F1:**
[figure not shown]
**Inclusion: Flow-chart**.

All surgical specimens undergo histological examination. If the histological findings verify a pathogenesis other than diverticulitis, the patient will be excluded.

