### Follow-Up

All follow-ups include haemoglobin, C-reactive protein, leukocyte count, presence of a stoma, re-admittance/s, re-operation/s. Clinical follow-up after discharge is scheduled at a minimum of 6-12 weeks, 6 months and 12 months. Patients randomised to the HP with planned stoma reversal are scheduled to have a follow-up at least 6-12 weeks following this procedure, regardless of the earlier follow-up plan from the primary operation. All patients undergo colonoscopy, computer tomography colonography or double contrast barium enema, within 12 months.

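### Histology-based exclusion after randomisation works differently in the two arms, because only Hartmann patients normally have an index specimen

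*Protocol article*

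**What the plan says.** All four points are in the Methods of the protocol article.

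- **Timing of allocation** (Randomisation and Surgical Procedure): "Patients are randomised when the diagnosis of diverticulitis Hinchey grade III has been confirmed". This happens during the diagnostic laparoscopy, before any specimen exists.
- **What each arm receives** (same section): Hartmann patients are "converted to open surgery followed by resection of the inflamed part of the colon and a diverting colostomy". For the other arm, "Patients randomised to lavage receive at least 3L of body-temperature, until return of clear fluid", followed by a drain. The Background describes lavage as a treatment that leaves the colon unresected.
- **The exclusion rule** (text after Figure 1): "All surgical specimens undergo histological examination". Then: "If the histological findings verify a pathogenesis other than diverticulitis, the patient will be excluded".
- **What happens to those excluded** (External Validity): "patients excluded after randomisation are registered", in the screening log. Their follow-up and analysis are not mentioned.

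The primary endpoint is re-operations within 12 months of the initial emergency operation (Endpoints).

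**The concern.** The rule acts on information that arises after allocation, and allocation determines who has that information. A Hartmann patient with another pathology is identified at once, whatever happens later. A lavage patient with the same pathology is identified only if later surgery yields a specimen, and otherwise stays in. The groups left after exclusion are no longer the groups that randomisation made comparable.

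Re-operation is also the primary endpoint. If re-operation specimens trigger the rule, exclusion in the lavage arm is tied to having had the event. With 40 patients per arm, one or two such patients can matter.

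**Working it through.** **1. The plan's own figure.** Inputs from Statistical Analysis: 40% v 10%, 80% power, 5% significance (taken as two-sided). With pooled variance and no continuity correction:

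n = [1.960 × √(2 × 0.25 × 0.75) + 0.842 × √(0.24 + 0.09)]² / 0.30² = 31.5, so 32 per group.

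This matches the article. At 40 per arm the power is 88.8%. With 36 in the Hartmann arm and 40 under lavage it is still 87.2%, so the issue is bias and not sample size.

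**2. Effect on the lavage rate if re-operation specimens count.** Let q be the share of randomised patients with another pathology, r their chance after lavage of a re-operation within 12 months that yields a specimen, and p the re-operation rate in true diverticulitis. The values of q and r are assumptions; p = 10% is the design rate.

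- All randomised: (1 − q)p + qr
- After the rule: (1 − q)p / (1 − qr)

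| q | r | All randomised | After the rule |
|---|---|---|---|
| 2.5% | 0.5 | 11.0% | 9.9% |
| 5% | 0.5 | 12.0% | 9.7% |
| 5% | 1 | 14.5% | 10.0% |
| 10% | 0.5 | 14.0% | 9.5% |
| 10% | 1 | 19.0% | 10.0% |

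The lavage rate falls by about 1 to 9 percentage points over this range.

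**3. Effect on the Hartmann rate, under either reading.** Let h be the re-operation rate in true diverticulitis and s the rate in those with other pathology. The rule changes the Hartmann rate from (1 − q)h + qs to h, a shift of q(h − s). With h = 40% and q = 5%, the shift is 0.05 × 0.40 = +2.0 points if s = 0, and 0.05 × (0.40 − 1) = −3.0 points if s = 1. The sign is not known in advance. The 40% planning rate includes many stoma reversals, so s need not be near zero.

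**4. Effect on the test.** Pooled two-proportion test (chi-square) and Fisher's exact test. The counts are assumed.

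| Hartmann v lavage | Who is removed | Chi-square p | Fisher p |
|---|---|---|---|
| 16/40 v 8/40 | nobody | 0.051 | 0.087 |
| 16/39 v 7/39 | 1 Hartmann without event, 1 lavage with | 0.025 | 0.046 |
| 15/39 v 7/39 | 1 Hartmann with event, 1 lavage with | 0.044 | 0.077 |
| 15/38 v 6/38 | 2 Hartmann (1 event), 2 lavage (both events) | 0.021 | 0.039 |
| 14/38 v 7/39 | 2 Hartmann with event, 1 lavage with | 0.063 | 0.077 |
| 15/39 v 8/40 | index specimens only: 1 Hartmann with event | 0.071 | 0.087 |

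These are illustrations and not bounds. Removing two Hartmann patients with events and no lavage patient (14/38 v 8/40) gives chi-square p = 0.099.

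**5. At the design rates.** 16/40 v 4/40 is a difference of 30.0 points, p = 0.002. Removing one Hartmann patient without an event and one lavage patient with an event gives 16/39 v 3/39: 33.3 points, p = 0.0006. Removing one Hartmann patient with an event on the index-only reading gives 15/39 v 4/40: 28.5 points, p = 0.003. The conclusion holds each time, but the estimate moves.

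**The case against.** **The sentence may concern only the index specimen.** It stands beside the inclusion flow chart and before Follow-Up, so it can be read as confirming eligibility. No lavage event would then be deleted. This stands as a possible reading, although "All surgical specimens undergo histological examination" has no such limit. The exclusion would still follow randomisation and would then affect essentially one arm only.

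**Exclusion is not defined as exclusion from analysis, and a full protocol or SAP may deal with it.** That is fair as to certainty. But the point is not an omission: the article states an affirmative rule, and the only provision for such patients is that they are registered.

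**The colon examination covers both arms:** "All patients undergo colonoscopy, computer tomography colonography or double contrast barium enema, within 12 months". It does not restore symmetry. The rule is tied to surgical specimens, and two of the three permitted examinations are imaging that gives no tissue.

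**Other routes to a lavage specimen exist.** Conversion at the index operation, or surgery after 12 months, could yield one without a primary event. Later surgery within 12 months is the main route and not the only one.

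**Numbers may be small.** Inspection of all four quadrants already removes some other pathology before randomisation, and the remaining prevalence is unknown. This limits the size and leaves the mechanism intact.

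A reader might infer that the rule necessarily favours lavage. The documents do not support that: on the index-only reading the direction is open, and even when lavage events are deleted the Hartmann rate may fall as well. In the 14/38 v 7/39 case the difference shrinks from 20.0 to 18.9 points. A reader might also infer that the rule hides the main harm of leaving the colon in place. The article does not rank harms in that way, and it requires the excluded patients to be registered.

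**Conclusion.** The rule as written is unsound: it excludes patients after randomisation, on evidence whose availability depends on the arm. That follows from the text and needs no assumed figure.

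Direction is conditional. If re-operation specimens count, each lavage exclusion on a specimen obtained within 12 months removes a primary event and lowers the lavage rate. If only index specimens count, other pathology leaves the Hartmann arm alone and the bias may run either way.

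Size rests on assumed prevalence and counts. A borderline result can be moved across 0.05 or away from it. It would be too strong to say that one exclusion per arm creates significance, since that depends on the starting counts, on whether the excluded Hartmann patient had an event, and on the test. A result at the design rates keeps its significance with a biased estimate.

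**What to change.** Replace the exclusion sentence with wording such as: *Patients in whom histology or a later examination shows another pathology remain in follow-up and in their allocated group for the primary and all secondary analyses. The finding is reported by arm. A sensitivity analysis, labelled as such, excludes patients on histology and states which specimens count.* Restore any patient already excluded and complete that patient's outcome data.

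The cost is a change of wording and the follow-up of a few more patients. The sample size stays at 80. The analysed population becomes Hinchey III as diagnosed at operation and not as proven by histology; that is the population which was randomised.

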### Follow-Up

All follow-ups include haemoglobin, C-reactive protein, leukocyte count, presence of a stoma, re-admittance/s, re-operation/s. Clinical follow-up after discharge is scheduled at a minimum of 6-12 weeks, 6 months and 12 months. Patients randomised to the HP with planned stoma reversal are scheduled to have a follow-up at least 6-12 weeks following this procedure, regardless of the earlier follow-up plan from the primary operation. All patients undergo colonoscopy, computer tomography colonography or double contrast barium enema, within 12 months.

### Health Related Quality of Life

All patients are asked to fill out a quality of life form on the day of discharge, 6 months and 12 months. This form includes parts of EQ5D, SF 36 [20] EORTC-C30 [17] and -CR38 [21]. The questions are focusing on bowel symptoms, stoma care, activities of daily living, health economic status and bowel related episodes requiring re-admittance or re-operation.

### Health Economics Assessment

A health economic analysis will be performed based on the information collected in the clinical record forms (CRF), based on the model presented by Björholt et al [22]. The model will be used in combination with sensitivity calculations to ascertain robust results.

### Data Collecting and Monitoring

The surgeon will fill out the CRF for the operation, and at each follow-up. The hospitalisation CRF is filled out by a nurse. Quality of life forms are filled out by the patient at discharge and at each follow-up. All CRFs and quality of life forms are returned to the trial coordinating centre at Sahlgrenska University Hospital, SSORG. All data from CRFs and quality of life forms are stored on a server, and kept within the Sahlgrenska University Hospital database. Only the principal investigator and the deputy principal investigator can by mutual consent extract data for analysis.

A safety committee of independent scientists not involved in the trial will analyse safety when half the intended accrual has been reached.

### Statistical Analysis

The only prospective study of the laparoscopic lavage operation so far reported (n = 92) a 1% occurrence of further surgery after the initial episode, whereas the other seven studies, all retrospective, varied between 0% and 100% reoperation, all of which were colon resections [18]. In our retrospective study [7] we found that 40% of the patients were re-operated for the same disease within a year, many of which were stoma reversals. To be able to detect a reduction from 40% to 10% in reoperations, each group must include at least 32 patients. The calculation is based on a binomial approximation, 80% power and a level of significance of 5%. In view of the relatively complicated flow chart for the trial and that all procedures are emergency surgery; the inclusion is set to 80 randomised patients (40 + 40).

Randomisation to blocks was generated using the Analysis Tool Pack in Excel, by the trial statistician. For each participating centre one block of 10 is sent at a time. The package consists of 10 closed envelopes, with numbers 1-10 on the outside, to be opened in sequence as the randomizations occur.

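### Blocks of 10 per centre, issued as numbered packages and published during recruitment, make some allocations in this open trial predictable when eligibility is judged

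*Protocol article*

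**What the plan says.** The protocol article describes the allocation scheme under Statistical Analysis. The list was prepared in blocks by the trial statistician: "Randomisation to blocks was generated using the Analysis Tool Pack in Excel, by the trial statistician". Supply is by centre: "For each participating centre one block of 10 is sent at a time". The form of supply is: "The package consists of 10 closed envelopes, with numbers 1-10 on the outside, to be opened in sequence as the randomizations occur".

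Under Randomisation and Surgical Procedure the ratio is given: "Randomisation is 1:1 to laparoscopic lavage and Hartmann's Procedure". So is the moment of allocation: "Patients are randomised when the diagnosis of diverticulitis Hinchey grade III has been confirmed". Patients with other grades leave the randomised trial at that point: "Hinchey grade I, II and IV are excluded from randomisation and treated according to local guidelines". One arm stays laparoscopic. The other is converted to open resection with a colostomy, so the team at a centre can see what each earlier envelope held.

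External Validity provides a screening log that also covers patients who were included but not randomised. The Discussion gives the state of recruitment: begun in February 2010, eight hospitals recruiting by March 2011 and three more ready, with completion intended by 2013.

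**The concern.** Concealment should ensure that whoever decides on eligibility cannot tell which arm comes next. Here the start, end and length of each block are visible on site, because one package is one block, and the length is also in print. A running tally of opened envelopes is enough to work out what remains, with no tampering.

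The decision this could influence comes immediately before the envelope. Grade III is randomised and grades I, II and IV are not, and a borderline finding needs judgement. The article names no independent assessor. That the operating team does the grading is an inference from the surgeon's role in deciding on surgery ("Emergency surgery decided by the attending surgeon") and in recording data ("The surgeon will fill out the CRF for the operation, and at each follow-up").

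At stake is comparability of the arms. If expectation of the next arm sways a borderline grade, milder or more severe peritonitis can collect in one arm. Severity is plausibly related to re-operation, the primary endpoint. The trial is small: at the planning rates of 40% and 10% it expects 16 and 4 patients with a re-operation among 40 + 40.

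**Working it through.** **The plan's own figure.** The article gives no figure for predictability. Its sample size reproduces with the two-sided pooled normal formula: n = [1.96 × √(2 × 0.25 × 0.75) + 0.842 × √(0.4 × 0.6 + 0.1 × 0.9)]² / 0.3² = (1.200 + 0.483)² / 0.09 = 31.5, so 32 per group. Predictability does not change this number; its harm is bias, not loss of power.

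**Inputs.** Ratio 1:1, block of 10 per centre and 80 patients are from the article. A 5:5 balance in every block is inferred from the ratio and the use of blocks. The number of centres is taken as 8 (recruiting) to 11 (with the three that were ready).

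**Allocations certain in advance, completed block.** Allocation j is certain when one arm's five envelopes are all among the first j − 1. There are C(10,5) = 252 equally likely orders, so the probability is 2 × C(j − 1, 5) / 252:

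| Position | Calculation | Certain |
|---|---|---|
| 6th | 2 × 1 / 252 | 0.8% |
| 7th | 2 × 6 / 252 | 4.8% |
| 8th | 2 × 21 / 252 | 16.7% |
| 9th | 2 × 56 / 252 | 44.4% |
| 10th | 2 × 126 / 252 | 100% |

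The sum is 420 / 252 = 1.67 per completed block. None of the first five is ever certain.

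**Correct guesses, completed block.** Always guessing the arm with more envelopes left gives, with k = 5, k + (4^k / C(2k, k) − 1) / 2 = 5 + (1024 / 252 − 1) / 2 = 6.53 of 10. By position the probabilities are 0.500, 0.556, 0.556, 0.595, 0.595, 0.643, 0.643, 0.722, 0.722 and 1.000, which add to 6.53.

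**Whole trial.** Many centres will stop inside a block, so the figures for completed blocks cannot simply be scaled up. If each patient is equally likely to come from any of m centres, the number at a centre is Binomial(80, 1/m). Summing the position probabilities over that distribution, with a new block after every tenth patient, gives:

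| Accrual (assumed) | Certain, of 80 | Guessed correctly |
|---|---|---|
| 11 centres, equal chance | 4.8 (6%) | 60% |
| 8 centres, equal chance | 8.3 (10%) | 62% |
| 8 full blocks (upper limit) | 8 × 1.67 = 13.3 (17%) | 8 × 6.53 = 52.3, or 65% |

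Uneven accrual over 11 centres, with weights proportional to 1/rank, gives 6.6 certain and 61%, inside this range. The most favourable case is an exactly even split over 11 centres: eight with 7 patients and three with 8. That gives 8 × 0.056 + 3 × 0.222 = 1.1 certain and (8 × 4.09 + 3 × 4.81) / 80 = 59% guessed. Such evenness is unlikely in emergency recruitment.

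**The case against.** The best defence is that the room for steering is narrow. All four quadrants must be inspected and the grade confirmed before randomisation. The criteria tie grades to observable markers: whether fluid is free in the abdomen and whether there is obvious faecal soiling. The log registers patients considered for emergency surgery, so selective exclusion leaves a trace. Emergency cases are presumably spread over time and over several on-call surgeons, which makes a tally less likely. Ten is also a fairly long block; a known fixed block of 4 would give 70.8% correct guesses. All of this limits the size of the problem. None of it removes the problem, because the markers leave borderline cases and the log works only after the event.

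The full protocol may describe opacity, sealing and custody of the envelopes. That is a fair answer to any complaint about the article's silence, and no such complaint is made here. Opaque envelopes would not help against a tally of a known block.

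A reader might infer more than the article supports:

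- *That 17% of allocations are known and 65% guessable.* This holds only if every block is completed. With 11 centres averaging about 7 patients, only about 19% of centres would be expected to fill a first block.
- *That unfinished blocks harm the trial by unbalancing the arms.* Power at 40% versus 10% is 88.8% with 40 + 40 and 88.2-88.7% with 36 and 44, depending on direction.
- *That sizing on an unstratified comparison is an error, or that a centre-stratified analysis is missing.* Unstratified sizing is common, and the analysis model may stand in an analysis plan that is not shown.

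**Conclusion.** The point holds, at modest size. The published scheme makes the last allocation of every completed block deducible and the ninth deducible in 44% of blocks. Over the trial, about 5 to 8 of 80 allocations would be certain in advance and about 60-62% guessable, with about 13 and 65% as the upper limit. Knowing the next arm is therefore confined to late positions in a block; earlier it is guessing somewhat better than chance.

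The figures rest on 5:5 blocks, on 8 to 11 centres with roughly similar recruitment, and on a team that keeps count. The article gives no evidence that any centre has steered patients, and it would be wrong to read the point as saying so. The weakness lies in what the article fixes: a visible block per centre, open treatment, and eligibility graded on site just before the envelope. Selection bias that enters this way cannot be reliably repaired in the analysis, so the scheme deserves changing while recruitment is under way.

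**What to change.** For all packages not yet sent, generate each centre's list from randomly varying block lengths that are not disclosed to centres or in print, and cut the packages without regard to block ends. The end of a package then no longer reveals an allocation. Require the Hinchey grade and the time to be recorded before the envelope is opened, so that the eligibility decision is fixed and can be checked against the screening log.

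The lengths should not be mostly short. Varying them takes away certainty, but favouring the arm that is behind needs only a tally and succeeds more often in short blocks: 66.6% for completed blocks of 8, 68.3% for 6 and 70.8% for 4.

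The cost is a new list from the trial statistician, one more entry at randomisation and slightly more logistics, with no extra patients. Packages already at centres stay predictable unless their unopened envelopes are replaced. With about 7 patients per centre, many centres would never need a second package, so replacement decides how much of the benefit is obtained.
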